## Abstract

**Background:**

Children with cerebral palsy (CP) often have communication impairments, including speech altered intelligibility. Multiple levels of disrupted speech have been reported in CP, which negatively impact on participation and quality of life, with increase of care needs. Augmentative Alternative Communication (AAC) is an option, with debated benefits and limitations, in particular for its functional use. This is supported by a substantial lack of defined evidences in favor of direct speech articulation intervention in CP. Motor learning-based interventions are effective in CP and are the basis of speech motor interventions such as PROMPT (Prompts for Restructuring Oral Muscular Phonetic Targets). The PROMPT speech motor treatment provides tactile-kinesthetic inputs to facilitate articulatory movements by dynamic modelling, resulting in more efficient motor patterns that can be integrated into speech and communication. In CP, exploratory evidences support the feasibility and preliminarily advantages on intelligibility of motor speech treatments, such as PROMPT, with increased speech motor control, also documented by kinematic analyses.

**Methods:**

A randomized waitlist-control trial will be conducted in children aged between 3- and 10-years having CP and dysarthria (estimated sample size = 60 children). Children will be allocated in the immediate intervention or in the waitlist control group. The intervention consists of an intensive 3 weeks period of twice-a-day administration of PROMPT. Standard care will be administered in the control (waitlist) group. After repeated baseline assessments (T0), the PROMPT treated group will undergo the experimental 3-week intervention period, with T1 assessment at the end. A further T2 assessment will be provided at medium term (3 months after the end of the intervention) for evaluating the stability of intervention. Primary and secondary speech clinical and kinematics outcome measures will be collected at T0, T1 and T2.

**Discussion:**

This paper describes the study protocol consisting of a RCT with two main objectives: (1) to evaluate the or short-term benefits of an intensive speech motor intervention on speech and intelligibility in children with CP and the stability of the intervention at medium term; (2) to describe the kinematic correlates of speech motor control modifications.

**Trial registration:**

Trial registration date 06/12/2019; ClinicalTrials.gov Identifier: NCT04189159.

## Background

Cerebral palsy (CP) is the most common cause of motor disability worldwide, with a prevalence of 2–2.5 per 1000 live births [1]. Several comorbidities distinguish the clinical picture of children with CP, such as communication impairment, feeding difficulties, intellectual disability, vision and hearing impairment and epilepsy. Communication difficulties in CP include altered phonation, low speech intelligibility, abnormal development of gesture and facial expression and receptive and expressive language impairment. Communication impairment has been identified in at least 40% of children with CP [2], with 36–90% of the children undergoing motor speech impairments [3–8]. Recent findings report up to 78% of dysarthria among children with CP and motor speech impairment [9]. However, multiple levels of disrupted speech, involving the development of sounds (articulation), the rules of sound combinations (phonology), phonatory support and the precise execution of speech movements (dysarthria) and their planning/programming (apraxia of speech) can be co-existing in CP [9], thus supporting the potential theoretical value of different intervention approaches and strategies [10, 11]. It has also been suggested that some children with CP who do not present clear symptoms of dysarthria, may still have speech motor control deficits [9, 12, 13]. Poor intelligibility due to motor speech impairments has a strong negative impact on daily life and personal autonomies, it reduces the quality of life and spreads daily care needs [7, 8]. Impaired speech abilities with severe reduction of intelligibility and effortful production are considered as a clue for augmentative alternative communication (AAC) to supplement or replace oral speech in CP, with debated advantages and limitations over AAC functional use [5]. The use of AAC approaches is in part supported by a substantial lack of evidences in favor of direct speech articulation interventions in children with CP [11], despite some preliminary advantages and a possible impact on intelligibility [11, 14].

Only few studies addressed the topic of providing evidence based, reproducible and targeted early interventions to improve speech motor abilities of children with CP. Though the limited evidences on efficacy compared to no treatment at all, it might be hypothesized that in general, motor learning principle-based interventions [15], are indicated for CP to improve also speech intelligibility, voice loudness and articulatory accuracy [14–16]. For instance, in a group of 7 children with spastic quadriplegia, Boliek and Fox [17] described some positive effects on vocal functioning, with limited stability of the benefits on intelligibility by using a motor speech treatment originally developed for adults with Parkinson disease, the Lee Silverman Voice Treatment (LSVT LOUD) [18, 19]. Interestingly, the behavioral changes described following this type of treatment were supported by changes in white matter integrity, as documented through a neuroradiological study of connectivity [20]. Less research has been dedicated to treatment protocols targeting the articulatory subsystem though there is clear evidence of substantial alterations at this level. Ward and colleagues [21] studied the effect of PROMPT (PROMPTs for Restructuring Oral Muscular Phonetic Targets) on articulation in a small group of children aged 3–11 years with different types of CP (dyskinetic, spastic, unilateral and bilateral). This approach, that is consistent with Dynamic Systems Theory (DST), proved effective in changing the speech motor patterns of children with CP, resulting in improved intelligibility and motor quality as documented by kinematic analyses [21]. At our knowledge, the previous papers are among the limited number of studies that investigated the effects of a treatment approach aimed at modifying articulation rather than the subsystems providing respiratory and phonatory support. The few studies that investigated the speech of children with CP through kinematic analyses [12, 22–24] support the presence of a malfunctioning speech motor control, particularly evident when the children’s speech motor systems are challenged by longer sequences and an increasing motor load. This is in agreement with the hypothesis of altered functional synergies involved in speech output in CP, due to abnormal muscular synergies and reduced sensory feedback to motor commands [12]. These physio-pathological hypotheses may suggest a potential therapeutic value of treatment protocols whose main target is the articulatory subsystem and which use tactile-kinesthetic inputs to enhance the speech motor skills of children with CP. Indeed tactile-kinesthetic support, such as provided in the PROMPT treatment [25–27], could enhance the sensory feedback and help to both constrain and facilitate the articulators’ movements through the dynamic modelling of more efficient motor patterns that can be integrated into language and, ultimately, into communication.

Based on previous literature and theoretical assumptions, we hypothesize that children with CP and dysarthria will benefit from a high intensity motor speech treatment based on PROMPT. For this purpose, we designed a wait-list control study by comparing a three-week intensive PROMPT speech motor treatment to standard care. Outcome measures will include motor speech clinical assessment and intelligibility rating, as well as objective kinematic measures of speech motor movements. The stability of the functional improvements will be assessed at medium term.

## Methods/design

### Study design

We plan a randomized trial on the effects of PROMPT therapy in children with CP using a wait-list control group (Table 1). Enrolled children will be randomized into either immediate treatment or wait-list-control group. This design allows every child meeting inclusion criterion to eventually receive the treatment, thus avoiding issues of equipoise.

**Table 1 Tab1:** Trial detailed information

Data category	Information
Primary registry and trial identifying number	ClinicalTrials.gov Identifier: NCT04189159
Date of registration in primary registry	06 December, 2019
Source(s) of monetary or material support	The Prompt Institute, USA
Primary sponsor	The Prompt Institute, USA
Contact for public queries	SF, MD, PHD [contact]
Contact for scientific queries	SF, MD, PHD [contact] IRCCS Fondazione Stella Maris, Pisa, Italy
Public title	PROMPT to Improve Speech Motor Abilities in Children with Cerebral Palsy: a wait-list control group trial
Scientific title	PROMPT to Improve Speech Motor Abilities in Children with Cerebral Palsy: a wait-list control group trial
Countries of recruitment	Italy
Health condition(s) or problem(s) studied	Speech motor intervention in children with cerebral palsy
Intervention(s)	Active comparator: *PROMPT speech motor intensive trial*
	Standard care
Key inclusion and exclusion criteria	Ages eligible for study: 3–10 years Sexes eligible for study: both Accepts healthy volunteers: no
	Inclusion criteria: infant and children aged 3–10 years; cerebral palsy; speech motor deficit with dysarthria; intellectually adequate or mildly disabled; adequate or mildly impaired comprehension skills; phonatory control/phonate on demand; Italian first or main spoken language
	Exclusion criteria: exclusive use of alternative augmentative communication; medical fragility of structural/anatomical malformations affecting speech production or preventing participation to intervention
Study type	Interventional
	Allocation: randomized intervention model. Single blind (outcomes assessor)
	Primary purpose: improve speech intelligibility
Date of first enrolment	February 2020
Target sample size	60
Recruitment status	Recruiting

Baseline assessment will be carried out after enrollment (T-1) and allocation (T0). In order to obtain reliable baseline speech motor measures, three subsequent assessments of verbal motor skills will be administered at T0 according to the evaluation protocol described in the *Intervention* section. Post-intervention assessment will be administered within 1 week from the end of the treatment (T1). A further stability effect assessment will be performed 3 months from post intervention assessment (T2) in the intervention group for stability assessment. The baseline and outcome assessments will be video recorded for subsequent analyses at each time point (T0, T1 and T2). An experienced speech and language pathologist (SLP), different from the treating therapist will score each time point assessments for data collection. The detail of the assessments per timeline is reported in Fig. 1.

**Fig. 1 Fig1:**
[figure not shown]
Schedule of study enrolment, interventions, and assessments. PROMPT: PROMPTs for Restructuring Oral Muscular Phonetic Targets. SC: standard care. VMPAC: Verbal Motor Production Assessment. ICS-ITA: Intelligibility in Context Scale. VSS: Viking Speech Scale. DDK: Diadochokinetic rate

### Participants

Parents will be asked to consent for the children participation to the study. All study activities will be carried out in the clinical and research institute, IRCCS Stella Maris Foundation, Pisa, Italy, by a PROMPT trained therapist (CR) with appropriate knowledge of the clinical research process.

Inclusion criteria: 1) age between 3 and 10 years; 2) a diagnosis of CP; 3) presence of speech motor deficits consistent with dysarthria; 4) normal nonverbal Intelligence Quotient (IQ) or mild intellectual disability with adequate or mildly impaired language comprehension skills 5) presence of volitional phonatory control and the ability to phonate on demand 6) Italian as the first or main spoken language in the child’s environment. Exclusion criteria: 1) use of alternative augmentative communication strategies as the only means of communication, 2) structural anatomical malformations impacting speech production, 3) medical fragility preventing the participation in the intervention.

### Sample size

Based on the yearly number of children referred to the recruiting center for clinical management and rehabilitation, we expect to reach a convenient final sample of 60 subjects with CP and motor speech disorders (including intervention and wait-list) over a 2 years period, by considering a conservative 20% attrition rate for clinical trials. Recruitment will be completed according to the standards of research consent, followed by group randomization by a team member other than the SLPs in charge of treatment and assessment.

### Randomization/blinding

Enrolled participants will be randomly assigned to immediate treatment or waitlist by the use of a random-generator software by a member of the research team specifically designed. The SLP who will score the recorded three timeline for primary outcome measures, as well as the researcher who will analyze kinematic measures will both be blinded to group assignment.

### Study procedure

Eligible children will be referred to the research team for recruitment. The investigators will provide parents/guardians information about the study procedures and request informed consent. Demographic data and other clinical measures, including brain Magnetic Resonance Imaging (MRI) data and co-morbidities, will be collected after participants’ parents/caregivers have provided informed consent. Assessments and procedures included in the study will be provided at IRCCS Stella Maris Foundation, Pisa, Italy.

### Intervention

Each child will receive a full cycle of PROMPT therapy lasting 3 weeks, with two sessions per day over five consecutive days each week. Each session will last 45 minutes. The treatment will be delivered by an experienced SLP with fidelity level adherence to PROMPT [28] treatment criteria and supervised by a PROMPT certified instructor (IP) In PROMPT intervention, goals are chosen to reflect the complex interactions among the physical-sensory, cognitive-linguistic, and social-emotional domains, consistently with the PROMPT systemic conceptual framework. The Motor Speech Hierarchy (MSH) is the speech production and intervention model used to select speech motor goals for intervention. These hierarchical speech motor goals are embedded into the cognitive-linguistic and social-emotional goals for the child. Visual, auditory and tactile-kinesthetic-proprioceptive cueing techniques are used to model speech production and to train the best possible speech motor patterns. In particular, tactile-kinesthetic inputs are used to enhance the sensory input and to facilitate the formation of sensory–motor pathways required for the acquisition and accurate production of speech movement patterns. The principles of motor learning, such as a session of blocked practice followed by randomized practice and considerations on the type of feedback provided to the child (Knowledge of Performance, and/or Knowledge of Results) are applied to intervention sessions depending on the child’s needs. The blocked practice session is generally delivered at the beginning of the session and then is followed by two-three interactive play-based activities during which the selected speech targets are practiced in a randomized fashion and in a functional interactive context. The blocked practice session can be divided into shorter pre-practice sessions delivered two-three times at different points over the treatment session in consideration of the age and compliance of the children. The interactive activities selected for the randomized practice are chosen based on the motivation and interests of the children and are specifically selected and/or adapted to meet their needs in terms of accessibility and ease of manipulation. Adaptive seating is provided for children with more severe challenges in postural control.

### Primary outcome measures

*Verbal Motor Production Assessment for Children (VMPAC)* [29]*:* a standardized motor speech assessment, which includes 5 subscales, where higher scores mean better performance: Global motor control (range 0–20); Focal oromotor control (range 0–26); Sequencing (range 0–46); Connected speech and language (range 0–45); Speech Characteristics (range 0–7). In Global Motor Control the structural and neuromuscular integrity of the oro-facial district, tone and strength are assessed. Focal oromotor control is the area in which motor control in speech and non-speech movements is assessed according to a developmental hierarchical model of speech motor control. Focal oromotor control in the VMPAC is evaluated in movements requiring control of jaw, labial-facial musculature and tongue on only one of the three planes of movements (vertical, horizontal and anterior-posterior) that define the functional space in which speech movements are executed. In the sequencing area, the VMPAC assesses the child’s ability to learn and control non-speech as well as speech sequences across several repetitions of the same targets. In Connected Speech and Language Control the quality of motor control is evaluated during the production of phrases in a picture description task. This area allows for the evaluation of movement patterns that occur during language production and of the interactions between language complexity and the increase of motor load in longer units. Speech Characteristics is an area in which the management of voice parameters, speech rate, prosody and resonance are taken into consideration.

*Phonetic Inventory*: repetition of 21 syllables containing all the Italian consonantal sounds. The children’s performances on this task will be compared to the reference data collected from a group of 40 typically developing (TD) children [30, 31].

*The Intelligibility in Context Scale - Italian version (ICS-ITA)* [32–34]. The ICS provides a speech intelligibility measure with ordinal scores ranging between 1 and 5, where higher scores mean better performances. The scale assesses the intelligibility in functional communication across different settings (home, school, peers, familiar and non-familiar people interactions). Thus, the ICS aligns with the Environmental Factors described in the International Classification of Functioning, Disability and Health: Children and Youth Version (ICF-CY, World Health Organization [WHO]).

*Viking Speech Scale (VSS)* [4, 35], an ordinal scale for intelligibility, with scores ranging between 1 and 4. Lower scores correspond to better performances. The VSS reliably classifies the speech performance of children with CP and is focused on the presence and the severity of the motor speech disorder affecting oral communication with familiar and non-familiar speakers. This scale was developed in the context of a 3 years research program sponsored by the European Community, aiming at the promotion of best practices in the classification of children with CP and at documenting variations in access to health care and in health outcomes.

### Secondary outcome measures

*Kinematic speech motor measures*. A kinematic analysis of facial movements during simple speech repetition tasks will be implemented ad hoc, by means of a non-invasive marker procedure. Such analyses aim to record the variations over time of 5 different metrics quantifying the movements of jaw and lips [12], thus assessing the mandibular and labial-facial control pre- and post-intervention. The procedure will be conducted as follows. The subjects will sit in front of a video screen and will be asked to produce the words included in a probe words list, either by spontaneously naming the pictures presented on the screen or on repetition of the examiner’s model. The probe words list consists of 40 Italian words accurately chosen with regards to their frequency in child vocabulary repertoire and to their motor characteristics. The probe words list was developed according to the Motor Speech Hierarchy (MSH) [36], which is the developmental model of speech motor acquisition and control at the basis of the PROMPT motor speech framework. The model illustrates a hierarchical development of seven speech subsystems: Stage 1: Tone, Stage 2: Phonatory Control, Stage III: Mandibular Control, Stage IV: Labial-Facial Control, Stage V: Lingual Control, Stage VI: Sequenced movements and Stage VII: Prosody. The selected words vary in terms of motor complexity required at each stage of the hierarchy. The inclusion of a wide range of syllables and words shapes, ranging from easy, monosyllabic production with simple intersegmental transitions to multisyllabic words, allows data collection from children with limited motor speech skills as well as from children who are more verbal. A dedicated software, developed ad hoc by Khymeia s.r.l., will help the management of the speech tasks schedule (the probe words list) for the kinematic analyses, and will help to detect and delete repetition of non-optimal speech tasks contaminated by non-speech movements, non-pertinent conversations, etc.

### Additional outcome measures

*Diadochokinetic rate*: Diadochokinetic rate (DDK), assessed by a maximum performance task consisting in the fast repetition of a two- and/or three-syllable nonsense sequence (i.e. /pata/ or /pataka/) over 20 sec. (“count by time” method). The performance on this task will be compared to that of the same above described 40 TD children. The DDK rate is a robust speech measure that can provide information on the speech motor abilities of a speaker and on movement limitations (such as speech rate and the range of movements of the articulators), as well as elements for a differential diagnose among different speech sound disorders [37].

*Maximum phonation time*: the phonatory duration during the production of an open vowel (i.e. /a/) on a single expiration. This measure provides information on the functioning of speech breathing and of the laryngeal subsystem. Children with CP are reported to have shorter phonatory duration compared to TD children [38] due to an abnormally small vital pulmonary capacity [39–41]. Reduced expiratory volumes can affect the amount of speech movements that can be superimposed to phonation and, therefore, to speech expiration, thus determining a very effortful production of speech and, from the listener side, decreased intelligibility.

### Statistical analyses

Descriptive statistics and baseline differences between group will be investigated. Changes in clinical speech primary outcome measures (T0-T1) will be calculated to assess the short-term effects of PROMPT treatment versus standard care (waitlist group). Stability of the effects will be assessed at T2 in the PROMPT treated group. Secondary outcome kinematic speech measures will be also calculated at T0, T1 and T2 and included in the analyses. Covariates such as type of neurological impairment, type/severity of brain lesion and age, will be included in the analyses. Parametric or non-parametric statistics will be applied according to variables characteristics and distributions. Post-hoc adjustment will be applied for multiple comparisons when needed. Multivariate statistics will be finally performed. Data imputation will be considered according to characteristics and relationship of missing variables. Statistical significance will be considered at *p* < .05.

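### The primary comparison rests on T0-T1 change, and the named covariates leave out the outcome's own baseline score

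*Protocol article*

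**What the plan says.** The Statistical analyses section of the protocol article defines the short-term primary comparison through change: "Changes in clinical speech primary outcome measures (T0-T1) will be calculated to assess the short-term effects of PROMPT treatment" relative to the waitlist group. On adjustment it says: "Covariates such as type of neurological impairment, type/severity of brain lesion and age, will be included in the analyses". On baseline comparability it says: "Descriptive statistics and baseline differences between group will be investigated". On the test family it says: "Parametric or non-parametric statistics will be applied according to variables characteristics and distributions". No model is named.

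The Study design section adds: "In order to obtain reliable baseline speech motor measures, three subsequent assessments of verbal motor skills will be administered at T0". It does not say how the three assessments form the T0 value. The repeat is stated for verbal motor skills only. The primary outcomes also include a phonetic inventory and two ordinal intelligibility scales, ICS-ITA (1 to 5) and VSS (1 to 4), and no repeat is stated for either scale.

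The Abstract says that primary and secondary measures are collected at T0, T1 and T2, so a baseline score exists for each primary outcome.

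**The concern.** In a randomised comparison of change, the baseline score is usually the strongest single predictor of the T1 score. Subtracting it is not the same as adjusting for it. Subtraction fixes its coefficient at 1, whereas the data would usually support a smaller value. Two consequences follow.

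- **Precision.** The variance of change is at least as large as the residual variance after regression on baseline, apart from the small cost of estimating the slope.
- **Chance imbalance.** If the arms differ at T0 by chance, unadjusted change over-corrects, and the arm that starts worse tends to look better at T1.

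Both matter here. The target is 60 children aged 3 to 10 years with any type of CP, and the number comes from referral volume. The Randomization/blinding section describes software-generated assignment and mentions no stratification. Several outcomes are also bounded: a child at the best VSS level cannot improve, so change depends on the starting level.

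**Working it through.** **Inputs from the protocol article:** 60 children in total; 20% attrition; three T0 assessments of verbal motor skills; significance at 0.05.

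**Assumptions, not in the documents:** 1:1 allocation; two-sided test; equal variance at each occasion; a common correlation r between any two occasions, taken from 0.5 to 0.9; a true difference of 0.5 SD for the power figures.

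**Plan's own figure.** The 60 has no effect size, SD or power behind it, so there is no power calculation to reproduce. If 60 is the final number, 20% attrition implies 60/0.8 = 75 enrolled. If 60 is the enrolled number, 60 × 0.8 = 48 complete. Arms of 30 and 24 cover completers of 60 and 48.

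**Formulas** (units of the single-occasion variance, m baseline assessments averaged):
- Variance of the baseline mean: Vb = (1 + (m − 1)r)/m
- Change from baseline: 1 + Vb − 2r
- Adjusted for baseline: 1 − r²/Vb

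| r | Change, m=1 | Adjusted, m=1 | Cut | Change, m=3 | Adjusted, m=3 | Cut |
|---|---|---|---|---|---|---|
| 0.5 | 1.000 | 0.750 | 25% | 0.667 | 0.625 | 6% |
| 0.7 | 0.600 | 0.510 | 15% | 0.400 | 0.3875 | 3% |
| 0.8 | 0.400 | 0.360 | 10% | 0.267 | 0.262 | 2% |
| 0.9 | 0.200 | 0.190 | 5% | 0.133 | 0.132 | 1% |

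Averaging three baselines cuts the change-score variance by one third at every r (for example 0.600 to 0.400). That step accounts for most of the possible gain on the verbal motor measures, and a change score can take it as well.

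**Smallest detectable difference,** 80% power, (1.960 + 0.842) × √(2V/n), at r = 0.7:
- 30 per arm: one baseline, 0.560 SD for change and 0.517 adjusted; mean of three, 0.457 and 0.450.
- 24 per arm: 0.626 and 0.578; mean of three, 0.511 and 0.503.

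**Power for a 0.5 SD difference, 30 per arm:**
- One baseline: 49% for change and 61% adjusted at r = 0.5; 70% and 77% at r = 0.7.
- Mean of three: 66% and 69% at r = 0.5; 86.5% and 87.5% at r = 0.7.

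**Chance imbalance.** With one baseline, unadjusted change is shifted by (1 − r) × imbalance. At r = 0.7 and 30 per arm, one standard error of imbalance is √(2/30) = 0.26 SD, a shift of 0.3 × 0.26 = 0.08 SD. With the mean of three, Vb = 0.8 and the slope is 0.7/0.8 = 0.875. One standard error is √(2 × 0.8/30) = 0.23 SD, so the shift is 0.125 × 0.23 = 0.03 SD.

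**Cost of the extra parameter.** Estimating the slope inflates variance by about 1/(N − 4): 1/56 = 1.8% at 60 and 1/44 = 2.3% at 48. With one baseline a net gain remains across the range (at r = 0.9 and N = 60, 0.190 × 1.018 = 0.193 against 0.200). Against change from the three-assessment mean, the trade is about even at r = 0.8 and slightly unfavourable at r = 0.9.

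**Sensitivity.** Suppose the T0 assessments correlate 0.9 with each other and 0.7 with T1. Then Vb = 2.8/3 = 0.933, change from the mean has variance 0.533, and the adjusted variance is 1 − 0.49/0.933 = 0.475, a cut of 11%.

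**The case against.** The strongest reply is that the article condenses a fuller protocol. The exact model, the full covariate set and the rule for combining the T0 assessments would normally be found there or in an analysis plan. That largely stands, and silence on those details is not held against the trial. What remains is that the article does state the analysis variable and does name covariates, and the baseline score is not among them.

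Four stronger readings are tempting, and the documents do not support them.

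- A reader might infer that change will be analysed unadjusted. The covariate list is worded as examples, and change with baseline as a covariate gives the same treatment effect as the adjusted T1 score, so calculating change does not rule out the better analysis.
- A reader might infer that the triple baseline is thrown away, and quote a 35% gain (0.3875 against 0.600 at r = 0.7). That holds only if T0 is a single reading. The stated purpose, "In order to obtain reliable baseline speech motor measures", points if anything towards using all three. It also cannot be carried over to ICS-ITA or VSS, for which no repeat is stated.
- A reader might infer that a rank test will drop the covariates. No rank test is named, and ordinal and non-parametric methods with covariates exist. Choosing by type of variable is reasonable when numeric and ordinal outcomes are mixed.
- A reader might infer significance tests of baseline differences. The text says only that differences will be investigated.

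It is also fair to say that adjustment is not guaranteed to gain at this size, as the slope-estimation cost shows.

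**Conclusion.** The point holds in a limited form. The stated primary comparison is on T0-T1 change, and the named covariates omit a score that is already collected and usually predicts the outcome best. Naming it would improve on the method as stated.

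The size depends on the outcome. With one baseline reading, variance falls by about 25% to 5% for r from 0.5 to 0.9; for ICS-ITA and VSS this is only a rough guide, because the formulas are for numeric scores. For verbal motor measures with T0 taken as the mean of three, the fall is about 6% to 1%, and the slope-estimation cost offsets it when r is high. The remaining benefit there is protection against chance imbalance. The common correlation, equal variances, 1:1 allocation and two-sided test are all assumed. Nothing here shows that the planned comparison would be invalid.

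**What to change.** State in the Statistical analyses section, or in the analysis plan before any comparison by arm, that:

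- each primary outcome at T1 (or its change) is modelled on arm, the baseline score of that outcome, age and the other covariates already named;
- for the verbal motor measures, the baseline score is the mean of the three T0 assessments;
- for ordinal scales such as VSS, the model is one that accepts covariates, for example proportional odds with the baseline level as a covariate.

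The cost is wording and one parameter per model, about 2% variance inflation at 48 to 60 children. No new data, visits or measurements are needed.
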